**Cardiovascular conditions**
ㆍMean arterial pressure (MAP) < 60mmHg or > 120mmHg ㆍSystolic blood pressure (SBP) < 90mmHg or > 200mmHg ㆍHeart rate (HR) < 50bpm or > 140bpm ㆍArrhythmias causing hemodynamic instability ㆍConcerns about new myocardial ischemia
**Neurologic conditions**
ㆍ Richmond agitation-sedation scale (RASS) scale ≥ 3 ㆍUncontrolled epilepsy
**Others**
ㆍActive bleeding, such as Gastrointestinal bleeding or Overt bleeding ㆍBody temperature such as ≥ 39° ㆍNeuromuscular blockage within 4 hours ㆍPain, severe nausea and vomiting ㆍVentilator asynchrony or risk of extubation or weaning of ventilator ㆍOpen wounds on the lower extremities ㆍFall ㆍRequest to stop exercising
**Catheter placement in the femoral artery or vein (for only exercise intervention)**
ㆍExtracorporeal membrane oxygenation of the femoral artery or the presence of an intra-aortic balloon pump ㆍPerm catheter inserted into the femoral vein

### Outcome measures

Baseline data will be measured prior to randomization, and follow-up data will be collected at ICU discharge, hospital discharge, and 1 and 3 months after hospital discharge. The following baseline clinical characteristics will be collected, shown in Table 3 [7, 23]: age, sex, weight, height, premorbid modified Barthel index, premorbid FAC, Acute Physiology and Chronic Health Evaluation (APACHE II) score [27], whether cardiopulmonary resuscitation (CPR) was performed within 24 hours before admission to the ICU, primary diagnostic category of ICU admission, and comorbidity, rehabilitation services after hospital discharge.

**Table 3 pone.0301368.t003:** Clinical examination items.

**Baseline clinical characteristics**
ㆍBasic information: age, sex, weight, heightㆍPremorbid modified Barthel index (MBI)ㆍPremorbid functional ambulation category (FAC)ㆍ The Acute Physiology and Chronic Health Evaluation (APACHE II) scoreㆍCardio-pulmonary resuscitation (CPR) within 24 hours prior to admission to the ICU •Primary diagnostic category of ICU Admission •Comorbidity •Geriatric disease
**Outcomes**
ㆍThe number and percentage of completed in-bed cycling/stepping sessions ㆍThe duration and percentage of in-bed cycling/stepping sessions ㆍThe number of cessations of in-bed cycling/stepping sessions
ㆍThe interval from ICU admission to the first session of in-bed cycling/stepping ㆍ The number and percentage of completed conventional rehabilitation sessions ㆍ The duration and percentage of conventional rehabilitation sessions ㆍ The number of cessations of conventional rehabilitation sessions ㆍ The number of adverse events ㆍ Level of consciousness: Richmond agitation-sedation scale (RASS), confusion assessment method for the ICU (CAM-ICU) ㆍ Mobility: functional ambulatory category (FAC), functional status score (FSS-ICU), short physical performance battery score (SPPB), de Morton Mobility Index (DEMMI), falls efficacy scale (FES), activities-specific balance confidence scale (ABC) ㆍMotor power: sum of Medical Research Council (MRC) score, hand grip strength (HGS) ㆍActivities of daily living (ADL): modified Barthel index (MBI) ㆍQuality of life (QOL): 36-item short form survey (SF-36) version 2.0 ㆍOthers: Pittsburgh rehabilitation participation scale (PRPS), days to initiate ambulation (FAC ≥2), mortality-28 days, duration of mechanical ventilation, length of stay in the ICU, length of stay in the hospital, concomitant occupational therapy and its application dose, concomitant pulmonary rehabilitation and its application dose

The outcomes listed in Table 3 are the number and percentage of completed in-bed cycling/stepping sessions, the duration and percentage of in-bed cycling/stepping sessions, and the number of cessations of in-bed cycling/stepping sessions, the interval from ICU admission to the first session of in-bed cycling/stepping, the number and percentage of completed conventional rehabilitation sessions, the duration and percentage of conventional rehabilitation sessions, the number of cessations of conventional rehabilitation sessions, the number of adverse events, the confusion assessment method for the ICU (CAM-ICU), Richmond agitation-sedation scale (RASS), de Morton mobility index (DEMMI), FAC, functional status score for the ICU (FSS-ICU), short physical performance battery score (SPPB), falls efficacy scale (FES), activities-specific balance confidence scale (ABC), sum of Medical Research Council (MRC) score, handgrip strength, modified Barthel index, 36-item short-form survey (SF-36) version 2.0, days to initiate ambulation (FAC ≥2), mortality-28 days, duration of mechanical ventilation, length of stay in the ICU, length of stay in the hospital, Pittsburgh rehabilitation participation scale (PRPS), concomitant occupational therapy and its application dose, concomitant pulmonary rehabilitation and its application dose.

The schedule of enrollment and assessment of the participants are shown in Fig 2. After ICU admission, patients are screened according to the inclusion criteria. After the screening, the guardians of patients who meet the inclusion criteria will be given an information sheet and asked to provide written consent to participate in the trial. Patients will be enrolled in the trial, given a trial-specific identification number, and randomly allocated to a group using a computer-generated random sequence that is listed prior to the start of the trial. After baseline evaluation, patients will be assessed at ICU discharge, hospital discharge, 1 month after hospital discharge, and 3 months after hospital discharge. Measurements 1 month after hospital discharge will be conducted by a visit and measurements 3 months after hospital discharge will be performed over the phone.

**Fig 2 pone.0301368.g002:**
[figure not shown]
SPIRIT schedule of enrolment, interventions, and assessments of the study. The outcomes are the number and percentage of completed in-bed cycling/stepping sessions, the duration and percentage of in-bed cycling/stepping sessions, and the number of cessations of in-bed cycling/stepping sessions, the interval from ICU admission to the first session of in-bed cycling/stepping, the number and percentage of completed conventional rehabilitation sessions, the duration and percentage of conventional rehabilitation sessions, the number of cessations of conventional rehabilitation sessions, the number of adverse events, CAM-ICU, RASS, FAC, FSS-ICU, DEMMI, FES, ABC, Sum of MRC, MBI, SF-36 version 2.0, PRPS, days to initiate ambulation (FAC≥2) and others. ICU: intensive care unit; D/C: discharge; FAC: functional ambulation category; RASS: Richmond agitation-sedation scale; CAM-ICU: confusion assessment method for the ICU; MRC: Medical Research Council; DEMMI: de Morton mobility index; FSS-ICU: functnal status score for the ICU; SPPB: short physical performance battery score; MBI: modified Barthel index; SF-36: 36-item short form survey; FES: falls efficacy scale; ABC: activities-specific balance confidence scale; PRPS: Pittsburgh rehabilitation participation scale.

Data are collected and recorded on a standard report form and all the recorded data will be entered into the web-based data system by the double-entry method. All errors will need to be corrected by crossing out, with the researcher’s signature and date.

### Adverse events

In this clinical trial, adverse events are all undesirable medical events that cause symptoms that were not observed before the start of the clinical trial, listed in Table 4. Predicted adverse events include falls, fractures, severe pain, endotracheal tube removal, arterial line removal, central line removal, arrhythmia, bradycardia, systolic blood pressure > 200 mmHg, systolic blood pressure < 90 mmHg due to hemodynamic instability during exercise, desaturation ≤ 88% due to respiratory instability during exercise and other minor adverse reactions, such as dyspnea, dizziness, tachypnea, and sinus tachycardia [7, 28, 29]. Predicted side effects are also classified as adverse events, and the severity of adverse reactions is classified into mild, moderate, and severe. The frequency of adverse events that are both relevant and irrelevant to the investigational device will be recorded. In the case of unexpected serious adverse events or other unintended trial interventions over the course of the study, we will report to the institutional review board. Data and safety monitoring will be conducted for every five-participant registration.

**Table 4 pone.0301368.t004:** Lists of predicted adverse events.

Adverse events
Fall •Fracture •Severe pain •Endotracheal tube removal •Arterial line removal •Central line removal •Arrhythmia •Bradycardia •Systolic blood pressure > 200 mmHg or < 90 mmHg due to hemodynamic instability during exercise •Desaturation ≤ 88% due to respiratory instability during exercise •Other minor adverse reactions such as dyspnea, dizziness, tachypnea, and sinus tachycardia

### Ethics approval and consent to participate

This study will be approved by the Ethics and Research Committee of the responsible institution (IRB number 2303-176-1419). The consent form for informed consent will be approved by the responsible ethics committee.

### Statistical methods

Statistical analysis in this study will be conducted using SPSS (version 25.0; IBM, Armonk, NY, USA). All statistical analyses will be performed for an intention to treat and a per protocol population. The outcomes of the continuous variables will be analyzed using Mann-Whitney U test, whereas the discontinuous variables will be analyzed using the chi-square test or Fisher’s exact test for variables between the two groups at the same time. Additionally, subgroup analysis will be conducted between the stratified groups Multiple imputation by chained equations algorithm will be used to handle missing data. The datasets analyzed and codes used for these analyses will be available from the corresponding author upon reasonable request.

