### Recruitment

Clinicians in the ICU at our hospital will collaborate to enroll patients for this clinical trial. Additionally, posters about this study are planned to be affixed on the noticeboard in front of the ICU, facilitating easy access to information regarding the clinical trial for representatives of patients. The principal investigator will provide a detailed explanation of the study to the participants’ legal representatives since most admitted patients are critically or severely ill. The study will not exclude patients who are likely to participate based on their socioeconomic status. This study is a pilot clinical trial to investigate the feasibility and safety of in-bed cycling/stepping exercise intervention and aims to recruit at least 24 participants. Assuming a 20% loss for death and a 15% loss for follow-up, the required sample size was 12 per arm to be recruited in this study.

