### Allocation

The computer-generated sequence will be generated on the website (https://mrcc.snuh.org) by an independent institution in our hospital. A computer-generated sequence will randomly allocate the two groups in this study. The stratified block randomization method will assign the randomization table to the control or intervention group at a 1:1 ratio. The use of mechanical ventilation will stratify the participants.

The group allocation will be performed by an independent researcher who is not involved in evaluating outcomes and will be concealed to physiotherapists who are engaged in assessing outcomes. The participants and in-bed cycling/stepping intervention provider will be instructed not to disclose the allocation to the evaluator. After the end of the clinical trial, blinding will be maintained until the input of evaluation data is completed. Any unblinding prior to clinical trials due to accidental or serious adverse events should be documented. To promote data quality for assessment and collection of outcomes, assessors will be well-trained.

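### Randomisation is stratified by mechanical ventilation but the named between-arm tests ignore it, which costs power on any outcome for which ventilation is clearly prognostic

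*Protocol article*

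**What the plan says.** In the Protocol article, the Allocation section states "The stratified block randomization method will assign the randomization table to the control or intervention group at a 1:1 ratio" and "The use of mechanical ventilation will stratify the participants". The Statistical methods section then fixes the comparison: "The outcomes of the continuous variables will be analyzed using Mann-Whitney U test", with chi-square or Fisher's exact test for the other variables, comparing the two groups at the same time point. Neither ventilation status nor a baseline value enters these tests. The one stated analytic use of the strata is that "subgroup analysis will be conducted between the stratified groups".

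The Outcome measures section says "Baseline data will be measured prior to randomization" and lists premorbid Barthel index, premorbid ambulation category and APACHE II among the items collected. The Recruitment section describes a feasibility and safety pilot that "aims to recruit at least 24 participants".

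**The concern.** Stratified randomisation forces the arms to be nearly balanced on ventilation status, so differences between ventilated and unventilated patients contribute almost nothing to the chance difference between arms. An unstratified test does not know this. It counts the spread between strata as noise, so its reference variance is too large whenever the strata differ on the outcome. The test then rejects less often than its nominal level under the null and misses real differences.

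For some listed outcomes a difference between strata is plausible on its face: duration of mechanical ventilation is the clearest, and ICU stay is another. With 12 per arm there is little power to give away. The subgroup sentence is a second difficulty. Its wording can be read as comparing ventilated with unventilated patients, which is not a randomised contrast, and comparisons within strata would rest on very few patients.

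**Working it through.** **Inputs from the protocol.** 1:1 stratified blocks; two strata (ventilated or not); 12 per arm, 24 in total; losses of 20% for death and 15% for follow-up.

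**Not stated, so assumed.** An even ventilation split, two-sided 5% level, normal outcomes with within-stratum SD 1, a true effect of 1 SD, and stratum gaps from 0 to 1.5 SD. The stated 12 per arm cannot be reproduced, because no effect size, power or evaluable target is given.

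**1. Why the test is conservative.** Take the analogous comparison of means. With equal strata a gap g apart, the variance within an arm is 1 + g²/4. Balanced strata make the true sampling variance of the difference depend only on the 1. The unstratified standard error is therefore too large by a factor √(1 + g²/4), and the actual size is P(|Z| > 1.96 × that factor):
- g = 0.5: factor 1.031, cut-off 2.02, size 4.3%
- g = 1: factor 1.118, cut-off 2.19, size 2.8%
- g = 1.5: factor 1.25, cut-off 2.45, size 1.4%

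**2. Simulation of the rank tests.** Six per arm per stratum, asymptotic tests. Plain is Mann-Whitney; stratified is van Elteren. Repeat runs agree to within about one percentage point.

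| Stratum gap (SD) | Type I error, plain / stratified | Power at 1 SD, plain / stratified |
|---|---|---|
| 0 | about 5% / 5% | 63% / 59% |
| 0.5 | about 5% / 5% | 60% / 59% |
| 1 | about 3% / 5% | 54% / 60% |
| 1.5 | about 1.5% / 4–5% | 42% / 60% |

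With an uneven split (9 and 3 per arm) and a 1 SD gap, power is 56% against 60%.

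**3. After the stated losses.** 12 × 0.80 × 0.85 = 8.16, or 12 × (1 − 0.35) = 7.8, so about 8 evaluable per arm, or 4 per arm per stratum. Power is 41% with either test at a 0.5 SD gap, 33% against 40% at 1 SD, and about 24% against 42% at 1.5 SD.

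**4. An extreme case: duration of ventilation.** Suppose the unventilated stratum stays unventilated and is scored zero, and that among ventilated patients every intervention patient has a shorter duration than every control. The 12 zeros share midrank 6.5. The intervention rank sum is 6 × 6.5 + (13 + … + 18) = 39 + 93 = 132, against 12 × 25/2 = 150 expected. The variance is 12 × 12 × 25/12 = 300; corrected for ties it is 300 × (1 − 1716/13800) = 262.7. So z = 18/16.2 = 1.11 and p is about 0.27. The ventilated stratum alone, at 6 against 6, gives an exact p of 2/C(12,6) = 0.002. This shows how far the loss can go under those assumptions; it is not a forecast.

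**5. Baseline values.** With no stratum gap and an assumed baseline-outcome correlation of 0.5, power is 0.60 for Mann-Whitney, 0.64 for a linear model with stratum, and 0.75 with stratum and baseline. So adding the baseline itself gains about 11 points. Mann-Whitney size in that setting is 0.042, against 0.044 for the exact test at 12 per arm with no covariate in play. Omitting baseline costs power and leaves size unaffected.

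**6. Subgroup cells.** 24 ÷ 2 strata ÷ 2 arms = 6 per arm per stratum as randomised, and about 8 ÷ 2 = 4 after losses, if the split is even. Exact Mann-Whitney power for a 1 SD effect is 30% at 6 per arm and 15% at 4. At 3 per arm the smallest two-sided p is 2/C(6,3) = 0.10.

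**The case against.** The strongest reply is that this does not touch what the trial is for. The Discussion identifies completed, timed and ceased in-bed cycling/stepping sessions as the outcomes that examine feasibility and safety. The control arm has no such sessions, so no between-arm test applies to them. Effectiveness is left to further study, and no power is claimed. That stands, and it limits the weight of the point. It does not remove it, because Statistical methods commits to between-arm tests and the listed outcomes include strength, mobility, daily living, quality of life and mortality.

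It also stands that the protocol gives no prognostic strength for ventilation and no reason for choosing it as the factor. Up to a 0.5 SD gap the stratified test gains nothing.

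Several stronger readings are tempting and are not supported:
- **That the error rate is invalid.** The departure is towards too few rejections. It loses efficiency and does not create false positives.
- **That ignoring baseline also makes the tests conservative.** Step 5 shows that it does not.
- **That the strata will be spent on underpowered significance tests.** The text says subgroup analysis and names no test or p-value for it.
- **That ventilated and unventilated patients will be compared with each other.** The wording allows this, but showing the treatment effect within each stratum is an equally natural reading.

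Finally, covariate adjustment is often left to an analysis plan that is not shown here. That is why baseline adjustment is only an option below. The unstratified tests are different: the protocol names them.

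**Conclusion.** The point holds in conditional form. The design stratifies by ventilation and the named tests do not. Where ventilation is clearly prognostic (a gap of about 1 SD or more), the unstratified rank test is conservative and loses about 6 points of power at 1 SD and 18 at 1.5 SD. At 0.5 SD or less there is nothing to gain. These figures assume 12 per arm, an even split, normal outcomes and a 1 SD effect. They were computed for the rank tests only; for categorical outcomes the same mechanism applies, but no size has been worked out.

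This is a matter of efficiency in the secondary between-arm comparisons of a pilot. It merits correction because the change is cheap, but it does not threaten the feasibility conclusions. The subgroup sentence needs rewording whichever meaning was intended, since cells of about 6 per arm, or 4 after losses, support description only.

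**What to change.** - For between-arm comparisons of continuous and ordinal outcomes, use a ventilation-stratified Wilcoxon (van Elteren) test, reported with a stratified effect estimate and 95% confidence interval.
- For categorical outcomes, use Cochran-Mantel-Haenszel or an exact stratified analysis, again with an estimate and interval.
- Optionally, adjust for the baseline or premorbid value where one is collected.
- Replace the subgroup sentence with a statement that the intervention-versus-control difference will be displayed descriptively within each ventilation stratum, with estimates and intervals and no claim of effect.

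The cost is a few sentences and a few lines of code. The statistical cost is about 4 points of power (63% against 59%) on any outcome for which ventilation turns out to be unrelated.

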**Discussion:**

This study is a pilot clinical trial to investigate the feasibility and safety of conventional rehabilitation with additional in-bed cycling/stepping in critically ill patients. If the expected results are achieved in this study, the methods of ICU rehabilitation will be enriched.

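### Safety is a named aim, but the only inferential analysis stated for the safety outcomes is a between-group difference test at 12 per arm, which cannot show that excess harm is small

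*Protocol article*

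**What the plan says.** The Recruitment section states the aim: "This study is a pilot clinical trial to investigate the feasibility and safety of in-bed cycling/stepping exercise intervention". The Discussion part of the abstract, the end of the Introduction and the main Discussion say the same. Recruitment also sets the size: the trial "aims to recruit at least 24 participants". It allows for losses of 20% (deaths) and 15% (follow-up) and concludes that "the required sample size was 12 per arm to be recruited in this study". Allocation is 1:1.

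Table 3 lists the number of adverse events and 28-day mortality among the outcomes. The Statistical methods section gives a single rule for comparing the arms. Continuous outcomes go to the Mann-Whitney U test, and "discontinuous variables will be analyzed using the chi-square test or Fisher’s exact test for variables between the two groups at the same time". No outcome is exempted, and no significance level is given.

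On the descriptive side, the Adverse events section grades severity as mild, moderate or severe and adds that "The frequency of adverse events that are both relevant and irrelevant to the investigational device will be recorded". It also provides for safety monitoring after every five participants. The main Discussion names completed sessions, session duration and cessations as the outcomes that examine feasibility and safety.

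**The concern.** A safety question asks how large the excess harm could still be, given the data. A difference test asks whether the data are incompatible with no difference. With 12 patients per arm, a non-significant result is compatible both with no harm and with substantial harm, so it does not answer the safety question. The article therefore does more than leave detail to another document. It assigns a method to the safety outcomes, and that method does not serve the stated aim.

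At stake is what can be said at the end. If the comparison of adverse events is reported as not significantly different, a reader may take that as support for safety and carry it into a larger trial. The data might still allow an event in a quarter or more of exposed patients.

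**Working it through.** **Inputs from the article.** 12 patients per arm, 1:1 (Recruitment, Allocation); chi-square or Fisher for discontinuous outcomes, Mann-Whitney U for continuous ones (Statistical methods).

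**Inputs assumed, because the article gives none.** Two-sided 5% level; control-arm share of patients with at least one event, 5% to 20%; a patient-level yes/no outcome. Table 3 lists a count, so the count case is checked separately.

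**Step 1. The plan's own figure.** The 12 per arm rests on no stated event rate, precision, level or power, so it cannot be reproduced. The stated losses leave about 8 per arm: 12 × 0.80 × 0.85 = 8.2, or 12 × 0.65 = 7.8. All 12 are used below, which favours the plan.

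**Step 2. What a difference test needs in order to react (no assumed rate).** With no event among 12 controls and *k* among 12 intervention patients, Fisher's two-sided p is 2 × C(12,*k*) / C(24,*k*).

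- *k* = 4: 2 × 495 / 10,626 = 0.093, not significant.
- *k* = 5: 2 × 792 / 42,504 = 0.037, significant.

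The uncorrected chi-square test, which the article also allows, reacts one event earlier. For *k* = 4 it gives 24 × 48² / (12 × 12 × 4 × 20) = 4.8, p = 0.028. The expected count in each event cell is then only 2, where Fisher is the usual choice.

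**Step 3. What 12 exposed patients can exclude (no assumed rate).** With no events, the exact (Clopper-Pearson) two-sided 95% upper limit is 1 − 0.025^(1/12) = 26.5%. With 1/12 it is 38.5%, and with 2/12 it is 48.4%. If only 8 patients are evaluable, 0/8 gives 1 − 0.025^(1/8) = 36.9%.

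**Step 4. Chance of missing a true increase (assumed rates).** All 13 × 13 possible tables were enumerated. The miss probability is 1 minus the sum, over tables with p ≤ 0.05, of the product of the two binomial probabilities.

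| Control rate | Intervention rate | Missed, Fisher two-sided | Missed, uncorrected chi-square |
|---|---|---|---|
| 5% | 15% | 98.7% | 94.8% |
| 5% | 20% | 95.9% | 88.2% |
| 10% | 30% | 90.5% | 80.2% |
| 10% | 40% | 76.7% | 61.3% |
| 15% | 45% | 78.3% | 63.6% |
| 15% | 60% | 49.3% | 31.9% |
| 20% | 60% | 60.8% | 43.2% |
| 20% | 80% | 18.8% | 8.9% |

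By Fisher's test, a tripling or quadrupling is missed between about 99% and 19% of the time. The low end belongs to 20% against 80%, an excess of 60 percentage points.

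**Step 5. If event counts are compared by Mann-Whitney.** Simulation at 12 per arm, with an assumed control mean of 0.2 to 1 event per patient, gives these approximate miss probabilities:

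| Increase | Poisson | Overdispersed (gamma-Poisson, shape 1) |
|---|---|---|
| Doubling | 55–90% | 80–90% |
| Tripling | 10–72% | 60–80% |
| Quadrupling | 1–50% | 40–70% |

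The size of the problem therefore depends on how the outcome is defined and how common events are. Under every scenario, a non-significant test still sets no limit on harm.

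**The case against.** The strongest reply has four parts.

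- **Non-significance is not declared to mean safety.** A reader might infer that a favourable safety conclusion could rest only on p > 0.05. The article does not support that reading. It plans to record the frequency and severity of events, to monitor every five participants, and to examine sessions and cessations. The in-bed cycling/stepping outcomes can only be summarised within the intervention arm, because controls do not receive it. These are descriptive routes to a safety statement. This part stands.
- **No single miss probability describes the trial.** A reader might take 77–91% as a property of the design. It holds only for a 10% control rate, a yes/no outcome and a two-sided 5% Fisher test. The article states no rate and no level, and the outcome it lists is a count. Its definition of adverse events is broad and includes minor reactions, so higher control rates are plausible. This part stands. For the same reason, non-significance cannot be called close to certain whatever the harm.
- **Intervals may be in the full protocol or analysis plan.** They may, and their absence from an article is not by itself a fault. But the article does name the test for these outcomes, and the point concerns the fit of that named test. This part limits the finding without removing it.
- **A pilot is not meant to have power.** True, and that is a reason to estimate rather than test.

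**Conclusion.** The point holds as a mismatch between the aim and the stated method. Safety is a named aim. The only inferential analysis stated for adverse events and 28-day mortality is a between-group difference test at 12 per arm, and no stated inferential analysis bounds the harm.

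The size that needs no assumed event rate comes from steps 2 and 3: an imbalance of 0/12 against 4/12 is not significant by Fisher's test, and even an event-free intervention arm leaves a true per-patient rate of up to 26.5% compatible with the data. The miss probabilities in steps 4 and 5 are illustrations that rest on the assumed rates, level and outcome definition.

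This is a cheap improvement. It does not invalidate the data to be collected, and it does not show that the investigators intend to read non-significance as safety.

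**What to change.** In the Statistical methods section, replace the between-group tests for the safety outcomes with estimation, or keep them and label them descriptive:

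1. Report by arm the proportion of patients with at least one adverse event, with at least one severe adverse event, and dead by 28 days, each with an exact (Clopper-Pearson) 95% confidence interval.
2. Report the between-arm risk difference for each, with a 95% confidence interval (Newcombe or exact).
3. State that the safety statement is read from the upper limits in the intervention arm and of the difference, and that a non-significant p-value will not be taken as evidence of safety.
4. State what 12 exposed patients can exclude (with no events, a true rate above about 26%), and limit the conclusion to preliminary safety.

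The cost is a few sentences, with no extra patients or data. The downside is a visibly less favourable safety statement, because the intervals will be wide.
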